##### Patient web survey

We use an electronic questionnaire to collect patient-reported data from patient participants on disease activity, joint involvement and severity, work impairment, quality of life, disability, experience of care, self-management, understanding of their RA, resource use and travel time and costs related to in-person rheumatology outpatients visits. The baseline assessment additionally includes patient demographics (year of birth, gender, ethnicity, smoking status, postcode (to derive level of relative socio-economic deprivation), income, educational attainment).

For the baseline assessment, all patient trial participants receive instructions for completing the questionnaire at the time of allocation (irrespective of allocation group). Follow-up assessments take place at 3, 6, 9 and 12 months post-allocation.

There is an additional online questionnaire at 6 months asking patient participants to share their thoughts on the benefits of a range of potential future developments/uses of integrated symptom tracking.

##### Paper case report forms

In addition to duplicating the items on the eCRF, the abovementioned paper CRF also includes follow-up assessments of healthcare professionals’ use of the interactive REMORA dashboard (if and at what time they viewed the tracked symptom data (e.g. before or during the clinic visit), and if and how it was useful/informed the consultation).

##### Interactive dashboard usage data (intervention group only)

We collect data on the date, time and duration of a user session for each occasion the interactive REMORA dashboard is opened. This data is supplied by the two providers of the regional data repositories (see element 4 in Fig. 2) in Greater Manchester and Northwest London and is extracted from their systems’ usage logs.

##### Symptom completion data (intervention group only)

Similar to previous phases of REMORA [15, 32], completion data for the daily, weekly and monthly questionnaires comes from the app data and is provided by the software team hosting and supporting the REMORA app.

##### Clinic observations

A member of the study team conducts in-person, non-participant clinic observations using an observation template that covers the length and process of the consultation, as well as completion of the OPTION5 tool to assess to what extent shared decision-making is happening [53]. For clinic visits with patient participants in the intervention group, we also explore if, how and when the patient-reported symptom data are reviewed and discussed. Visits are audio-recorded if patient and healthcare professional have consented to this; else, the observer takes notes. Audio-recordings are transcribed verbatim by a professional secretarial service.

##### Interviews

All interviews are individual and semi-structured. A member of the study team conducts interviews in-person or via telephone or video conferencing, depending on participant preference. Interviews are expected to last between 30 min and 1 h and cover a range of topics, depending on the participant type (see supplementary Table S4 for further details on interview topics). Where possible, we use purposive sampling to maximize variation of interviewees’ characteristics (e.g. age, gender, ethnicity, intervention, engagement level). The interviewer audio-records the interview where consent has been given or else takes notes. Audio-recordings are transcribed verbatim by a professional secretarial service.

#### Plans to promote participant retention and complete follow-up

Most strategies used to promote participant retention and complete follow-up are outlined under ‘Strategies to improve intervention uptake and adherence (i.e. intervention fidelity)’*.* In addition, patient participants receive a combination of up to three email and text reminders to complete each patient web survey. Patients currently on trial receive quarterly patient newsletters, with content developed by our PPIE group.

#### Data management

##### Data collected at site

As described above, clusters collect data using paper and electronic CRFs. All eCRFs are hosted and stored on REDCap, a secure, web-based platform designed to support research data capture. Paper CRFs are transcribed into electronic format by delegated cluster staff and stored on site. The cluster’s local principal investigator is responsible for ensuring the accuracy, completeness, legibility and timely provision of the data reported in the (e)CRFs.

##### Data collected directly from patient participants

The online survey for collecting patient-reported data is hosted on REDCap, with some of the questionnaire items also being collected via the REMORA smartphone app by patient participants allocated to integrated symptom tracking.

##### Data collected through interviews and observations

Where consent has been given, all interviews and observed clinics are audio-recorded using an encrypted device and transferred to secure servers at the earliest opportunity. Study team members may create written field notes on paper (e.g. if consent to recording is not offered, or to provide additional context to discussions). Paper notes are scanned, stored on the secure servers and then destroyed as soon as practically possible.

#### Confidentiality

We regard all personal data collected as part the REMORA2 trial as confidential, and no information allowing (direct or indirect) identification of individuals is released into the public domain. One measure to ensure confidentiality is the REMORAid. This is a unique participant identifier (or trial number) we assign to all participants, comprising a two-letter site code and a randomly generated five-digit number. Patient participants in the integrated symptom tracking group use the REMORAid to set up the REMORA app prior to submitting their first symptom report, while the study team use it to internally link participant-level data throughout the trial.

Furthermore, the programme manager, delegated cluster staff and the study team maintain all essential documents in a way that facilitates management, audit and inspection of the study. Essential documents are documents that individually and collectively permit evaluation of the conduct of the study and substantiate the quality of the collected data. Any essential documents required to be held by the co-principal investigators are stored by the study team so that these are readily available, upon request, to the regulatory agency and sponsor for the minimum period as required by the regulator and UK Law. Medical files of patient participants are retained in accordance with national legislation.

All essential documents are securely stored, with access restricted to authorized personnel. Direct access is granted to restricted members of the study team involved in data management and analysis, as well as appropriate IT and governance staff at the sponsor institution.

#### Plans for collection, laboratory evaluation and storage of biological specimens for genetic or molecular analysis in this trial/future use

No biological specimens are collected for analysis in this trial or for future use. We only obtain laboratory values of inflammatory markers obtained at hospital sites as part of usual care.

### Statistical methods

#### Statistical methods for primary and secondary outcomes

This section summarizes the planned statistical methods for the primary and secondary quantitative outcomes listed in Table 1. For all analyses described below, we will take an intention-to-treat approach, i.e. we will include participants in the treatment group they are assigned to regardless of the extent to which they take up or adhere to the intervention. Further details, including on methods for qualitative outcomes, will be provided in the full statistical analysis plan, which we will draft with input from the trial’s programme steering committee and publish before we lock the trial data set.

We will report the trial results in accordance with the CONSORT stepped wedge trial extension [60].

##### Primary outcome analysis

The primary analysis will use a generalized linear mixed-effects regression model, with DAS28-CRP at 12 ± 3-months follow-up as the outcome [61, 62]. Model predictors include DAS28-CRP at baseline, follow-up length (in days) and intervention (standard of care or integrated symptom tracking), complemented with further relevant prognostic factors. We will include cluster as a random effect and report the ICC of the linear mixed effects models alongside model coefficients. We will report effect estimates as 95% confidence intervals and consider intervals excluding a null effect as statistically significant. As there is only a single primary outcome of interest, we will not adjust at the type-I error level.

Since our continuous outcome short exposure design means that each participant only receives one intervention, we are not expecting any carry-over effects.

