**Fig. 1 Fig1:**
[figure not shown]
Stepped wedge cluster randomized controlled trial design. Healthcare professionals are primarily recruited during an 8-week run-in period (healthcare professional recruitment only; weeks − 8 to 0). All clusters recruit patients for a total of 27 weeks (6.2 months). All sequences initially recruit to clinic visits offering standard of care (control group). In pairs of two (i.e. sequences), clusters are randomly allocated to switch to clinic visits offering integrated symptom tracking (intervention group). All patient participants are followed up for 12 ± 3 months from the time of their allocation

Recruited patients are allocated to receiving either clinic visits with standard of care (i.e. control) or visits with integrated symptom tracking (i.e. intervention) depending on the period in which they are recruited; they continue to receive the clinic visit type they are initially allocated to, including after their cluster has switched over.

Patient participants have at least one baseline and one follow-up visit at 12 months. The final follow-up visit falls within 3 months either side of the 12-month follow-up date to allow for routine outpatient visit scheduling. The rheumatology teams may schedule additional clinic visits during the follow-up period in accordance with usual clinical practice; we will include the data from these additional visits in the analyses.

As part of a hybrid effectiveness-implementation study design [34], we gather information on implementation through the parallel process evaluation. For this, we invite patient participants, healthcare professionals, people involved in implementing integrated symptom tracking, and those eligible but declining trial participation to take part in interviews and/or observations.

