#### Assignment of intervention: allocation and blinding

##### Sequence generation

As illustrated in Fig. 1, the 16 clusters are randomly assigned a site letter (A-P) by the programme manager independently of the trial statistician. Using computer-generated simple randomization, the trial statistician independently and randomly allocates letters A-P to eight sequences, numbered 1–8. The numeric order of the sequences reflects the order in which clusters switch over from standard of care to integrated symptom tracking, with sequence 1 switching over after the first 3-week period and sequence 8 at 24 weeks for the eighth and final step.

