### Outcomes

#### Primary outcome

As shown in Table 1, the primary outcome (to address objective 1) is a difference in the marginal mean disease activity score (DAS) as measured on the DAS28 with C-reactive protein (DAS28-CRP), at 12 ± 3 months follow-up between the standard of care and the integrated symptom tracking groups, after accounting for covariates (including baseline DAS28-CRP, study site, follow-up length and others). The DAS28 is a composite disease activity score that incorporates information about swollen joints, tender joints, acute phase response and global assessment [43]. It is used widely in clinical practice and clinical trials and forms the foundation of internationally accepted treatment response criteria [44]. The DAS28-CRP is a subset of the DAS28, which uses the CRP blood test result to derive the composite score. We opted for CRP rather than erythrocyte sedimentation rate (an alternative blood test for calculating DAS28) based on what was most used by participating hospital sites.

**Table 1 Tab1:** Outcomes per objective, including measurement variables, data collection methods, and analysis metrics

Objective	Outcome	Measurement variable	Data collection method	Analysis metric

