*CDAI* Clinical Disease Activity Index for RA, *CollaboRATE* share decision making questionnaire, *COM-B* Capabilities, Opportunities, Motivations for Behaviour change questionnaire, *CRF* Case report form, *DAS28-CRP* Disease Activity Score for 28 joints using C-reactive protein, *EHR* Electronic health record, *EULAR* European Alliance of Associations for Rheumatology, *EQ-5D-5L* EuroQol five-dimension scale questionnaire, *HAQ* Health Assessment Questionnaire, *IPQ* Illness Perception Questionnaire, *PEI* Patient Enablement Instrument, *RA* rheumatoid arthritis, *RAID* Rheumatoid Arthritis Impact of Disease score, *RAPID-3* Routine Assessment of Patient Index Data 3, *SJC28* Swollen Joint Count for 28 joints, *TJC28* Tender Joint Count for 28 joints, *WPAI-RA* Work Productivity and Activity Impairment questionnaire: Rheumatoid Arthritis

^a^For remote consultations, we collected a CDAI score [47] instead of a DAS28 as calculation of the former does not require a blood test

^b^After accounting for measured variables that improve estimate precision, including cluster and outcome assessment at t0 (i.e. baseline); t4 is the time of final follow-up at 12 ± 3 months

^c^Our PPIE group developed a ‘Checking your tender and swollen joints’ section on the study’s website [38] with instructions and a training video for patients on how to self-assess and count tender and swollen joints

^d^Medication use at baseline includes past (i.e. previous 6 months) and current exposures, with any changes to RA medication recorded at all subsequent follow-up visits

^e^Includes number and dates of in-person rheumatology consultations and related travel time/costs, telephone rheumatology consultations, general practitioner consultations and hospital admissions

^f^Related to in-person rheumatology outpatients visits

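### The published primary model names no recruitment-period or calendar-time term, although recruitment period determines allocation in this stepped wedge

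*Protocol article*

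**What the plan says.** The protocol article's trial design section (text with Fig. 1) allocates patients to control or intervention "depending on the period in which they are recruited". Sequence generation fixes the schedule, "with sequence 1 switching over after the first 3-week period and sequence 8 at 24 weeks for the eighth and final step", and the Fig. 1 legend gives the total length: "All clusters recruit patients for a total of 27 weeks (6.2 months". That makes nine 3-week periods.

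The adjustment set appears in three places:

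- Primary outcome analysis: "Model predictors include DAS28-CRP at baseline, follow-up length (in days) and intervention (standard of care or integrated symptom tracking", then "complemented with further relevant prognostic factors". On random effects: "We will include cluster as a random effect and report the ICC of the linear mixed effects models alongside model coefficients".
- Primary outcome: "after accounting for covariates (including baseline DAS28-CRP, study site, follow-up length and others".
- Table 1, footnote b, which covers the primary and the comparative secondary outcomes: "After accounting for measured variables that improve estimate precision, including cluster and outcome assessment at t0 (i.e. baseline".

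None of the three names period, step, recruitment date or calendar time. The only time-related issue that the analysis section discusses is carry-over. The planned sensitivity analyses concern engagement and missing data. Continuous secondary outcomes are to be analysed much like the primary one.

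**The concern.** In a stepped wedge the share of patients on intervention rises with calendar time, here from 0% in the first period to 100% in the last. Anything that moves DAS28 over the same months (season, staffing, prescribing, early versus late recruits) is therefore partly confounded with the intervention unless the model contains time.

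The named covariates do not do this job. Follow-up length counts days since allocation: two patients with equal follow-up recruited 24 weeks apart have their outcomes 24 weeks apart. The open clause refers to prognostic factors, and footnote b gives precision as the purpose of adjustment. Period is a different kind of variable, because it determines allocation.

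At stake is the trial's single confirmatory test, and with it the secondary models that follow the same form.

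**Working it through.** **Inputs.** From the sample size section: difference 0.6, SD 1.2 (variance 1.44), ICC 0.05, cluster auto-correlation 0.8 with discrete time decay, 16 clusters in 8 steps, and 432 analysed (27 per cluster, so 27/9 = 3 per cluster-period). From the design: 9 periods. Two-sided 5% is taken from the 95% confidence interval rule. The drift sizes are assumptions, since the protocol gives none.

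**1. The plan's own figure.** I used generalised least squares with categorical period effects and, for each cluster, covariance of period means 1.44 × [0.05 × 0.8^|j−k| + (0.95/3 if j = k)]. The treatment SE is 0.173. Power = Φ(0.6/0.173 − 1.96) = Φ(1.51) = 93.4% (89.7% with a t reference on 14 df). This agrees with the stated figure of at least 90% with 432 patients, so the sample size is consistent with a period-adjusted analysis.

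**2. Overlap of group and time.** Numbering periods 0 to 8, the mean period is 2.33 for control and 5.67 for intervention, a gap of 3.33 periods (10 weeks). Within every cluster the gap is 4.5 periods (13.5 weeks). The correlation between group and period is 0.645.

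**3. Share of a linear drift that leaks without a period term (random intercept for cluster).** Let a cluster have s control periods, s = 1 to 8, with two clusters for each s.

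- Within-cluster sum of squares of the intervention indicator: 2 × Σ s(9−s)/9 = 2 × 120/9 = 26.67.
- Between-cluster sum of squares: 2 × 9 × Σ (s−4.5)²/81 = 18 × 42/81 = 9.33.
- Within-cluster cross-product with a drift running from 0 to 1: 26.67 × 4.5/8 = 15.0.
- Weight on between-cluster information: 0.95/(0.95 + 27 × 0.05) = 0.413.
- Leak = 15.0/(26.67 + 0.413 × 9.33) = 15.0/30.52 = **0.49**.

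The leak runs from 0.42 (ICC near 0) to 0.52 (ICC 0.10). A single mid-recruitment shift leaks about 0.66 of its size. A wave symmetric about mid-recruitment leaks nothing.

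**4. Standard errors of that model.** Model-reported SE = √[(0.95 × 1.44/3)/30.52] = √0.01494 = 0.122. The true sampling SE under the time-decay structure is 0.132.

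**5. Consequence when there is no true effect.** With bias b = 0.4915 × drift, type I error = Φ[(−1.96 × 0.122 − b)/0.132] + 1 − Φ[(1.96 × 0.122 − b)/0.132].

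| Assumed drift over recruitment (DAS28 points) | Bias | Type I error |
|---|---|---|
| 0 | 0 | 6.9% |
| 0.1 | 0.05 | 8.8% |
| 0.2 | 0.10 | 14.7% |
| 0.3 | 0.15 | 24.4% |

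A drift of 0.3 thus gives a bias of about a quarter of the 0.6 target (0.15/0.6).

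**6. With period in the model.** The bias from a drift common to all clusters is zero. The SE is 0.173 whether period is categorical or linear, although the linear form removes only linear drift.

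**The case against.** The strongest defence is that the lists are open. The predictors are said to include certain items, others are to be added, and the section describes itself as a summary. Detail is left to a full statistical analysis plan, to be drafted with a steering committee that includes an independent statistician with stepped wedge expertise. The article also commits to the CONSORT stepped wedge extension. Nothing excludes period. This stands as a limit on the claim: a reader might infer that the trial will be analysed without period, and the document does not show that. It does not dispose of the point. The article spells out follow-up length and omits, in all three places, the one time variable that the design requires.

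Two further readings are tempting and should not be drawn.

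- *All drift becomes treatment effect.* It does not. About half of a linear drift leaks, a symmetric pattern leaks nothing, and baseline DAS28-CRP absorbs part of any drift already present at recruitment. The figures above include no baseline adjustment. Baseline would not capture changes in care after recruitment, and the categorical secondary models leave baseline out.
- *The confidence interval is far too narrow because period is missing.* Setting 0.122 against 0.173 compares two different estimators. The model SE of 0.122 should be judged against its own sampling SE of 0.132: about 7% too small. That shortfall comes from ignoring time decay in the cluster correlation. The harm from omitting period is bias, and it arises only if there is drift.

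It is also fair to say that no drift is documented and that the size of the harm is conditional on it.

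**Conclusion.** The point holds as a badly fixed model statement. The published primary model, the primary-outcome definition and Table 1 footnote b name no period or calendar term, while allocation is set by recruitment period. Followed as written, about 49% of a linear drift over the 27 weeks enters the treatment coefficient. At assumed drifts of 0.1 to 0.3 points this means bias of 0.05 to 0.15 and a type I error of about 9% to 24%, against 6.9% with no drift. Falling DAS28 would imitate benefit and rising DAS28 would hide it.

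The figures rest on the protocol's ICC, auto-correlation and SD, on equal recruitment of 3 analysed patients per cluster-period, on drift common to all clusters, and on no absorption by baseline. The conclusion concerns the published text. The statistical analysis plan is not shown and may already contain the term.

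**What to change.** Name recruitment period as a fixed effect, either categorical with nine levels or as a prespecified function of recruitment date, in four places: the primary model, the primary-outcome definition, Table 1 footnote b and the secondary models. Add a cluster-by-period or time-decaying random effect to match the correlation structure used for the sample size. With period added but only a random intercept, the model SE is 0.171 against a true 0.176 (type I error about 5.6%), so most but not all of the mismatch would be gone. If the statistical analysis plan already contains these terms, the remaining step is to align the published wording. A sensitivity analysis on the calendar date of the outcome visit is optional.

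The cost is wording and precision. Recruitment timing is already recorded, since it defines allocation. The SE rises from a model-reported 0.122 to about 0.173. At 432 analysed this still gives about 93% power by the normal approximation, so the change by itself needs no more patients. The choice should be fixed before data lock, because adding the term after results are known would be a post hoc decision that could alter the conclusion.

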##### Sample size

The accepted minimal clinically important difference for effect of a direct novel disease modifying therapy for RA is a change of 1.2 points on the DAS28 [57]. As our intervention is modifying disease indirectly, we are anticipating a smaller target difference of 0.6 points in the DAS28, with an expected standard deviation of 1.2 [57].

In the absence of established methodology for sample size calculations for trials with a continuous recruitment short exposure design, we used the ShinyCRT calculator [58, 59] with the cross-sectional design setting to produce a conservative (i.e. greater) sample size estimate. We estimated that we needed to include 432 patient participants in the analysis (i.e. 27 participants per cluster) to achieve at least 90% power for detecting the target difference under the following assumptions: a discrete time decay within-cluster correlation structure; varying cluster sizes with a coefficient of variation of cluster size of 0.15 (based on accruing roughly 27 ± 4 patient participants per cluster); a between-groups a type-I error rate (alpha) of 0.05; an intra-class correlation (ICC) of 0.05; a cluster auto-correlation of 0.8; and 16 clusters switching over in pairs of two across eight steps. In the absence of available shared datasets and published trials relevant to ours, we formulated our assumptions regarding the ICC and cluster auto-correlation in consultation with the clinical trial design expert on the REMORA2 programme steering committee (see under ‘ Oversight and monitoring’ below), who advised on commonly used and relatively conservative figures that would give us ample sample size in a range of potential scenarios.

Based on findings from the feasibility trial [32], we anticipate 30% of recruited patient participants allocated to the intervention group may not initiate symptom tracking, with a further 15% across both groups being lost to follow-up due to drop-out/withdrawal. To compensate for this attrition and achieve the required analysis sample size of 432, we aim to recruit a total of 736 participants (i.e. 46 per site).

There are no formal interim analyses planned, thus we do not anticipate any adjustments to the sample size.

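### The primary model names one constant cluster random effect, but the sample size assumes within-cluster correlation that decays over time; if it does decay, intervals are somewhat too narrow

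*Protocol article*

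**What the plan says.** The Sample size section assumes "a discrete time decay within-cluster correlation structure" with "an intra-class correlation (ICC) of 0.05; a cluster auto-correlation of 0.8", 16 clusters and eight steps. It arrives at an analysis sample of 432, or 27 in each cluster, and the stated aim is "to achieve at least 90% power for detecting the target difference". It describes the correlation figures as commonly used and relatively conservative. They were chosen on expert advice because no relevant data were available.

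The Primary outcome analysis section describes a mixed-effects model for DAS28-CRP at follow-up. Its named predictors are baseline DAS28-CRP, follow-up length and intervention, with further prognostic factors to be added. On correlation it says: "We will include cluster as a random effect and report the ICC of the linear mixed effects models alongside model coefficients". The decision rule is: "We will report effect estimates as 95% confidence intervals and consider intervals excluding a null effect as statistically significant".

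The Statistical methods part names no cluster-by-period term, decaying random effect, robust variance, small-sample correction or sensitivity analysis for the correlation structure. Continuous secondary outcomes are to be analysed in a similar way to the primary outcome.

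**The concern.** A single cluster random effect fixes the auto-correlation at 1. Under the sample-size assumption, the correlation between two patients of one cluster is 0.05 within a period. Between the first and last of nine periods it is 0.05 × 0.8^8 = 0.05 × 0.168 = 0.008. A stepped wedge relies heavily on before/after comparisons within clusters. A model that takes the cluster effect to be constant gives those comparisons too much precision when the effect actually drifts.

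Significance rests only on whether the 95% interval excludes the null, so the coverage of that interval is the trial's type I error control. The planning section allows for decay, and the analysis as stated then leaves it out.

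**Working it through.** **Inputs.** From Sample size: difference 0.6, SD 1.2 (variance 1.44), alpha 0.05, ICC 0.05, auto-correlation 0.8, CV of cluster size 0.15, 16 clusters in 8 sequences, 432 analysed. From the legend of Fig. 1: 27 weeks of recruitment, so 27/3 = 9 periods and 27/9 = 3 patients per cluster-period. Two-sidedness is inferred from the 95% interval rule.

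**Step 1: reproduce the plan's figure.** The covariance of cluster-period means is 1.44 × (0.05 × 0.8^|s−t| + I × 0.95/3). Generalised least squares with fixed period effects gives SE = 0.173.
- Normal reference: power = Φ(0.6/0.173 − 1.96) = Φ(1.51) = 93.4% (93.2% with CV 0.15).
- t on 16 − 2 = 14 df: 89.7% (89.4% with CV 0.15).

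The stated figure is reproduced on the normal reference.

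**Step 2: large-sample effect of the structure alone.** A random-intercept model with period effects is fitted when the truth is decay. At 3 per cluster-period the model SE is 0.166 and the true SE 0.1735, so the model SE is 1 − 0.166/0.1735 = 4.3% too small. Type I error = 2Φ(−1.96 × 0.166/0.1735) = 6.1%. At about 5 per cluster-period it is 7.0%. When the true correlation is constant it is 5.0%.

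**Step 3: simulation with 16 clusters.** Random-intercept REML, period effects fitted, true decay (ICC 0.05, auto-correlation 0.8), no treatment effect, 6,000 runs per row (Monte Carlo error about 0.3 points):

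| Per cluster-period | Model SE | Empirical SE | Shortfall | Rejection, normal | Rejection, t on 14 df |
|---|---|---|---|---|---|
| 3 | 0.164 | 0.176 | 6.8% | 7.1% | 5.0% |
| 4 | 0.145 | 0.158 | 8.2% | 7.5% | 5.4% |
| 5 | 0.132 | 0.146 | 9.6% | 8.0% | 5.7% |

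A separate 10,000-run simulation at 3 per cluster-period gave SE 0.164 against 0.175 (6.3% too small), with rejection of 6.9% (normal) and 4.7% (t on 14 df).

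**Step 4: separate the two causes, at 3 per cluster-period.** A decay-structured model fitted to the same truth rejects 5.9% with a normal reference and 3.9% with t on 14 df. With the normal reference, the small number of clusters therefore adds 5.9 − 5.0 = 0.9 points, and the wrong structure adds 6.9 − 5.9 = 1.0 point. When the truth is one constant cluster effect, the random-intercept model with a normal reference rejects 5.5%. At about 5 per cluster-period the structural share is larger (Step 2).

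**Step 5: analysed numbers and range.** The plan states 27 analysed per cluster, which is 3 per cluster-period. A figure of 46 × 0.85/9 = 4.3 follows only if the 46 recruited per site lose 15% and non-initiators stay in under intention to treat; the protocol does not state it. As an assumed large-sample range at 3 to 5.1 per cluster-period:
- ICC 0.01: 5.1 to 5.5%
- ICC 0.05, auto-correlation 0.5 to 0.95: 5.4 to 7.5%
- ICC 0.10: 5.8 to 10.3%

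**The case against.** The section calls itself a summary and defers further detail to a SAP, to be published before data lock. The steering committee that contributes to it includes an independent statistician with stepped wedge expertise. Naming cluster as a random effect does not exclude other random terms, and a degrees-of-freedom method is ordinary SAP content. All of this stands, and it means the repair is still open. It does not remove the inconsistency: the random effect and the single ICC are positive statements, and they differ from the structure used for the sample size.

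A reader might infer that the standard errors are wrong and that the type I error exceeds 5% as a matter of fact. The document does not support that. The decay values are planning figures chosen without data, and under constant correlation the structural inflation is nil. Nor does the protocol commit to a large-sample Wald interval; it names no interval method, so the 7 to 8% is conditional on a normal reference. With t on 14 df the stated random-intercept model is close to nominal at the plan's ICC. Rates near 10% belong to ICC 0.10, twice the planned value.

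The calculations also include period effects, which the protocol does not name, and omit baseline adjustment, which it does. Adjustment will change the residual variance and the ICC, and no figure is given for that.

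**Conclusion.** The point holds, at modest size. The analysis model as stated is not the one on which the trial was sized. Assuming decay at ICC 0.05 and auto-correlation 0.8, with period effects fitted, its SE is about 6 to 10% too small at 3 to 5 analysed patients per cluster-period. The type I error is about 7 to 8% with a normal reference and about 5 to 5.7% with t on 14 df. The structure and the missing small-sample correction contribute about equally at the planned 3 per cluster-period, so correcting only the structure would still leave 5.9%. The continuous secondary outcomes inherit the same mismatch. This should be corrected before data lock, but it does not invalidate the design.

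**What to change.** In the primary analysis text and the SAP:
- Make the primary random structure match the sample size: cluster-by-period effects with discrete time decay.
- Fix the fallback in advance: on non-convergence use nested exchangeable (cluster plus cluster-period), then a cluster intercept.
- Name a small-sample correction: Kenward-Roger, Satterthwaite, or t with clusters minus 2 df.
- Report both the ICC and the cluster auto-correlation.

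The cost is wording, code, a fallback rule and slightly wider intervals. At 3 per cluster-period, decay with t on 14 df gave 3.9% rejection, so error is controlled, slightly conservatively. Power at 432 analysed falls from about 93% on the normal reference to about 89.7% on t with 14 df, just under the stated 90%. The power statement should be rechecked on the chosen reference distribution.
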